## Abstract

**Introduction:**

Head and neck cancer (HNC) affects the mouth, throat, salivary glands, voice box, nose or sinuses. Every year, over 12 000 people in the UK are diagnosed with HNC. Neck dissection is a key, surgical component of patient care. However, many people experience postoperative restriction in shoulder and neck movements, pain, fatigue and low mood, with only half ever returning to work.

**Methods and analysis:**

Getting Recovery Right After Neck Dissection (GRRAND) is a two-arm, multicentre, pragmatic randomised controlled trial. The trial aims to compare clinical and cost-effectiveness of a personalised physiotherapy programme (GRRAND programme) versus usual practice, National Health Service (NHS), postdischarge care.

The planned sample size is 390 participants. Participants will be recruited from across UK sites and followed up for 12 months. The primary outcome is the shoulder pain and disability index at 12 months. Economic evaluation will be conducted from a healthcare system and personal social services perspective. Secondary outcome data, including pain, function, health-related quality of life, mental well-being, health resource use and adverse events, will be collected at 6 weeks, 3, 6 and 12 months, with exercise adherence at 6 weeks. A process evaluation will determine how GRRAND is implemented, delivered and received across clinical settings, exploring what works, for whom and under what conditions. Analysis will be on an intention-to-treat basis and reported inline with the Consolidated Standards of Reporting Trials statement.

**Ethics and dissemination:**

The trial was approved by the London-Brent Research Ethics Committee (ref: 24/LO/0722) on 15 October 2024. Trial results will be disseminated via peer-reviewed publications, presentations at national and international conferences, in lay summaries and social media. This protocol adheres to the recommended Standard Protocol Items: Recommendations for Interventional Trials checklist.

**Trial registration number:**

ISRCTN13855775.

STRENGTHS AND LIMITATIONS OF THIS STUDYThis will be the largest randomised controlled trial assessing a physiotherapy intervention to usual care for people after neck dissection for head and neck cancer.The process evaluation uses a comprehensive approach to examine implementation, delivery and contextual factors, enhancing understanding of how the Getting Recovery Right After Neck Dissection programme works in real-world settings.The intervention framework is flexible, offering the ability for personalised tailoring of physiotherapy, avoiding a rigid standardisation of provision.Capacity to deliver physiotherapy when this is not usual care may provide a barrier for some hospitals to participate.

## Introduction

 There is a global increase in head and neck cancer (HNC) incidence, attributed in part to the impact of the human papillomavirus (HPV).^1^,^3^ Annually, HNCs are diagnosed in 700 000 people worldwide, with over 12 000 new cases each year in the UK.^2^ These cancers affect the mouth, throat, salivary glands, larynx, nose and/or sinuses. The incidence of HNC has increased rapidly in the UK over the last 20 years, in particular, in the oropharynx where the role of HPV has led to a doubling in disease incidence.^4^ It is expected to increase until, at least, 2045.^5 6^ People affected by HNC are now younger and more active.^7 8^

The treatment pathway for HNC is complex due to the varied anatomical sites of disease and patient needs. While treatment may involve a single modality of surgery, radiotherapy, chemotherapy or chemo–radiotherapy, many require multimodal approaches. Neck dissection is the most common component of surgical treatment both as primary treatment and following any disease relapse. It involves surgical removal of at-risk lymph nodes in the neck.^9^ The aim of surgery is to visualise and extract lymph nodes harbouring, or at risk of harbouring, tumour.

Despite improved treatments, functional morbidity remains a long-term problem, which impacts on people’s health-related quality of life (HRQoL) and with economic societal/health service consequences. Side effects from a neck dissection can be debilitating and disabling. They include neck and shoulder problems, difficulties sleeping, fatigue and generalised anxiety.^10 11^ Postoperatively, neck dissection surgery is associated with both early and late complications. Shoulder dysfunction is by far the most common and occurs in at least half and sometimes in all patients reported in different surgical series in the literature.^12^,^15^ Over 30% of people still experience shoulder pain and reduced function 12 months postoperatively.^16^ Where shoulder and musculoskeletal pain and dysfunction appear as late complications, these can persist for 5 years and beyond.^17^ The sequelae of shoulder dysfunction and psychosocial complications are strongly associated with reduced return to work. Up to half of people report an inability to work after treatment due to shoulder disability alone.^18 19^ Psychosocial complications are also highly prevalent postoperatively, predominantly anxiety and depression, but people also experience fatigue, social isolation and body image issues.^20^

Currently, there are no national guidelines for postoperative rehabilitation after neck dissection for HNC. Physiotherapy and rehabilitation provision in the UK is not uniform.^21^ Where service provision exists in the NHS, practice is varied and includes acute respiratory care, range of motion exercises for the neck and shoulder and advice on positioning the upper limb and shoulder girdle. A booklet or leaflet may be provided to supplement this treatment.^21^ Outpatient treatment is minimal and often reactive, with patients being referred by their General Practitioner (GP) or hospital clinical team only once a problem has been identified.^22^

We previously developed and tested a structured physiotherapy programme called Getting Recovery Right After Neck Dissection (GRRAND).^23^ In this feasibility study, we randomised 36 participants undergoing a neck dissection for HNC from two NHS hospitals to receive usual NHS care versus usual NHS care *PLUS* a structured, personalised, physiotherapy-led programme (the GRRAND programme). Our feasibility study demonstrated: (1) the GRRAND programme was feasible to deliver and was acceptable to patients and NHS staff; (2) a signal with respect to improved postneck dissection shoulder/arm function, pain and HRQoL and (3) the supportive rehabilitation booklet was acceptable.^23^ While this feasibility study demonstrated that a full trial was feasible for delivery in NHS settings, clinical and cost-effectiveness had yet to be determined.

### Aims and objectives

The aim of this trial is to determine whether a personalised physiotherapy-led rehabilitation programme (the GRRAND programme) or usual practice, NHS, postdischarge care is clinically effective and cost-effective approach for improving health-related outcomes in adults after neck dissection for HNC.

## Methods and analysis

### Trial design

GRRAND is a multicentre, pragmatic randomised controlled trial with 1:1 allocation, integrated health economic evaluation and process evaluation. The trial will include a 6-month internal pilot to test detailed trial procedures, data collection and confirm the feasibility of recruitment and conduct. Participants will be followed over 12-months postrandomisation to assess shoulder function, HRQoL, adverse events (AEs) and to collect cost data for economic evaluation. The trial will be conducted in NHS hospital settings. Sites will be selected to reflect demographic and socioeconomic diversity. Priority will be given to sites serving areas with high proportions of ethnic minority populations (especially Black communities) and areas of socioeconomic deprivation, including coastal communities.

This protocol article was written following the Standard Protocol Items: Recommendations for Interventional Trials guidelines.^24^
Figure 1 is the participant flow diagram. The participant consent form is presented (online supplemental file 1). A summary of core trial information is presented in the WHO trial registration dataset (online supplemental file 2).

**Figure 1 F1:**
[figure not shown]
GRRAND participant flow diagram. CRF, case report forms; EARS, exercise adherence rating scale; GRRAND, getting recovery right after neck dissection; EORTC, European Organization for Research and Treatment of Cancer; SPADI, shoulder pain and disability index; SWEMWBS, short Warwick–Edinburgh mental well-being scale.

### Patient and public involvement (PPI)

PPI has been essential in designing the trial and will continue to be critical in its delivery and dissemination. We have collaborated with a PPI group who have had neck dissection for HNC to understand their experiences, but also to inform our trial design. Two of these PPI representatives are coapplicants on the research team. Our PPI coapplicants are integral to the Trial Management Group (TMG), attending trial management meetings, contributing to trial processes, procedures and documentation, and they will be key to our dissemination plan. A further patient partner has joined the Trial Steering Committee (TSC).

### Objectives

#### Primary objectives

To compare the clinical effectiveness of the GRRAND programme versus usual practice, NHS, postdischarge care, on participant-reported shoulder pain and function 12 months after randomisation using the shoulder pain and disability index (SPADI).To compare the cost-effectiveness of the GRRAND programme against usual practice, NHS, postdischarge care from an NHS and personal social services perspective.

#### Secondary objectives

To evaluate postoperative pain, function, HRQoL, mental well-being, resource use and AEs at the following timepoints after randomisation based on:

SPADI total score and pain and disability domains at 6-weeks and 6-months postrandomisation.^25^EORTC (European Organization for Research and Treatment of Cancer) cancer-specific questionnaires (C30 (core))^26^ and H&N35 (head and neck specific)^27^ at 6-weeks 6- and 12-months postrandomisation.EQ-5D-5L^28^ at 6-weeks 3-, 6- and 12-months postrandomisation.Exercise adherence Rating Scale (EARS)^29^ at 6-weeks postrandomisation.Short Warwick–Edinburgh mental well-being scale (SWEMWBS)^30^ at 6-weeks 6- and 12-months postrandomisation.Health resource use questionnaire at 6-weeks 3-, 6- and 12-months postrandomisation.AEs and postoperative complications at 6-weeks 3-, 6- and 12-months postrandomisation.

To conduct a multimethods, process evaluation to examine trial processes, implementation fidelity and contextual factors are influencing delivery and engagement. This includes assessing mechanisms of impact, such as exercise adherence using the EARS,^29^ and synthesising quantitative and qualitative data to explore what works, for whom and in what contexts.

### Outcome measures

The schedule of enrolment, interventions and assessment can be found in online supplemental file 3.

#### Primary outcome

The primary outcome is the SPADI (total score) 12-months postrandomisation.^25^ This is a 13-item participant-reported shoulder-specific instrument (0–100 and 100 worst score).^25 31^ The SPADI consists of two dimensions: pain and disability (functional activities). The pain dimension consists of five questions designed to measure the severity of an individual’s pain. The disability dimension consists of eight questions designed to measure the degree of difficulty that an individual has with various daily activities. The SPADI total score can also be obtained as a weighted average of the two domains score. It has been widely used in previous shoulder, neck and upper limb trials^32 33^ and was considered to best measure the issues that mattered most to them following a neck dissection (ie, shoulder function). It has been shown to be responsive to change in both surgical and non-surgical intervention trials.^34^

#### Secondary outcomes

Secondary outcome measures are as follows:

SPADI total score^25^ at 6-weeks and at 6-months postrandomisation.SPADI total score^25^ for the pain and disability domains at 6-weeks 6-months and 12-months postrandomisation.EORTC QLQ-C30^26^ at 6-weeks 6-months and 12-months postrandomisation.EORTC QLQ-H&N35^27^ at 6 weeks, 6-months and 12-months postrandomisation.Mental well-being using the SWEMWBS^30^ at 6-weeks, 6-months and 12-months postrandomisation.Exercise adherence using the EARS^29^ at 6 weeks for both groups in addition to the last GRRAND physiotherapy appointment for those allocated to the GRRAND programme.EQ-5D-5L^28^ at baseline, 6-weeks, 3-months, 6-months and 12-months postrandomisation.Health resource use questionnaire at 6-weeks, 3-months, 6-months and 12-months postrandomisation.AEs and postoperative complications using the Clavien–Dindo Classification^35^ at 6-weeks, 3-months, 6-months and 12-months postrandomisation.

Process evaluation measures will include the number of staff trained, pre- and poststaff training knowledge and confidence with delivering structured HNC physiotherapy, the schedule and setting of session delivery (inpatient, outpatient or virtual), hospital and intervention case report forms (CRFs), including surgical procedure and spinal accessory nerve integrity, and observational checklists from site visits to assess fidelity.

#### Safety outcomes

AEs and serious adverse events (SAEs) related to the trial postconsent will be recorded on the appropriate CRF for return to the Warwick Clinical Trials Unit (WCTU) Team and reported to the relevant oversight committees. Further surgery, apart from the index intervention, will be considered an outcome. Treatment AE or SAE related to concomitant care, such as chemo- or radiotherapy, will not be considered recorded AEs. Persistent pain without new pathology or another event will not be considered an AE, as it will be recorded in outcome scores. SAEs will be followed up until the end of the 12-month follow-up period. All AEs and SAEs will be managed in accordance with WCTU’s standard operating procedure (SOP).

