#### Group 2: usual postoperative care

There is currently no standard treatment across the UK for rehabilitation following neck dissection for HNC.^21 42^ Accordingly, we consulted with the Clinical Advisory Group and the findings from our national survey^21^ and feasibility study^23 43^ to ensure the content and delivery of a usual practice intervention for this patient group reflects usual, NHS care.

The ‘usual care’ is based around the following four areas.

Advice to practise simple range of motion exercises for the face, neck and shoulder impacted by neck dissection, for the purpose of preventing the onset of postsurgical contracture and optimising the functions of swallowing and shoulder girdle movement.Respiratory care, targeting the functions of sputum clearance and breathing control.Mobility assessment to ensure safe hospital discharge.Education on body positioning to reduce pressure and drag on the shoulder girdle, oral health to reduce food pocketing in the mouth and pain management to optimise levels of comfort and function.

As a part of ‘usual care’ prior to hospital discharge, the ward physiotherapist will provide participants with a Hospital Discharge Booklet detailing postoperative, self-management strategies inline with the standards currently used in these settings. No routine outpatient or follow-up physiotherapy will be provided as per current, best, usual NHS care.^21^

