### Concomitant recovery treatments

In accordance with the pragmatic nature of this trial, participants will not be asked to desist from receiving other forms of treatment during the trial or follow-up periods. These may include contact with their GP, physiotherapist or other health professional, changes in medication or use of alternative therapies or treatments. Use of these treatments will be recorded through the health utilisation questionnaire at each follow-up period. The frequency of participants in the control group receiving physiotherapy will be reported to the oversight committees.

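### The exclusion of harms from concomitant care is not limited to anticancer toxicity, so harm from outpatient physiotherapy can be recorded in GRRAND sessions but left out when it arises outside allocated care

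*Protocol article*

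**What the plan says.** *Safety outcomes* contains two rules on what is recorded. The first is a relatedness filter: "AEs and serious adverse events (SAEs) related to the trial postconsent will be recorded on the appropriate CRF". The second is an exclusion: "Treatment AE or SAE related to concomitant care, such as chemo- or radiotherapy, will not be considered recorded AEs". The exclusion names no arm and gives two anticancer treatments as examples.

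Other treatment during the trial is described under the heading "Concomitant recovery treatments". Participants in either arm may have it: "These may include contact with their GP, physiotherapist or other health professional, changes in medication or use of alternative therapies or treatments". The section then deals with capture of use: "Use of these treatments will be recorded through the health utilisation questionnaire at each follow-up period". It adds: "The frequency of participants in the control group receiving physiotherapy will be reported to the oversight committees".

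Outpatient physiotherapy has a different status in each arm. In *Group 1*, up to six outpatient sessions over 6 months are the trial intervention. In *Group 2*: "No routine outpatient or follow-up physiotherapy will be provided as per current, best, usual NHS care". Ward physiotherapy, exercise advice and the discharge booklet are allocated care for controls, and the GRRAND arm receives this inpatient package too.

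*Secondary outcomes* lists "AEs and postoperative complications using the Clavien–Dindo Classification" at 6 weeks and 3, 6 and 12 months. *Safety reporting, AEs and SAEs* sets collection from randomisation to 12 months. Neither section repeats or overrides the exclusion.

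**The concern.** A harm comparison needs the same event to be counted by the same rule in both arms. Here the wording lets the count depend on who delivered the physiotherapy, and the allocation largely decides who delivers it.

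The exposure is plausible. The *Introduction* describes NHS outpatient physiotherapy as minimal and often reactive, arranged after a problem has been found. Control-arm physiotherapy is to be monitored, and the *Process evaluation* samples interviewees partly on use of external physiotherapy. The description of the GRRAND resistance exercises also anticipates symptom flare-up.

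At stake is the between-arm comparison of adverse events that physiotherapy or exercise could cause, which is part of a secondary outcome in a trial whose participants are unblinded. Events that were never recorded cannot be recovered in the analysis. The SPADI comparison is not affected.

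**Working it through.** **Step 1: the sections side by side.**

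| Source of a harm | Status of that care | Under *Safety outcomes*, read literally |
|---|---|---|
| GRRAND outpatient session | Trial intervention (*Group 1*) | Trial-related, so recordable |
| Ward physiotherapy, exercise advice, booklet (both arms) | Allocated care (*Group 2*, also given in *Group 1*) | Not touched by the exclusion |
| Outside physiotherapy, control participant | Listed under *Concomitant recovery treatments* | Excludable; may also fail the relatedness filter |
| Outside physiotherapy, GRRAND participant | Same | Same |

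The rows differ by source, not by arm. But a control participant can receive outpatient physiotherapy only from outside, whereas in the GRRAND arm it is the allocated treatment.

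**Step 2: inputs for an illustration.** The only usable figure in the protocol is 195 participants per group (*Power and sample size*). It follows from the stated inputs: 292 / 0.75 = 389.3, taken up to 390, and 390 / 2 = 195. The other inputs are assumptions:
- r, the risk of a physiotherapy-related event per recipient, equal in both arms: 2% to 10%;
- c, the share of controls who have outside physiotherapy: 10% to 50%;
- all GRRAND participants are treated, none has outside physiotherapy, and every control event from outside physiotherapy is excluded.

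**Step 3: formulas.**
- GRRAND events recorded = 195r
- Control events that occur = 195cr; recorded = 0
- Share of all such events lost = 195cr / (195r + 195cr) = c / (1 + c)
- True risk difference = r(1 − c); recorded = r; ratio = 1 / (1 − c)

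**Step 4: results.** GRRAND records 195 × 0.02 = 3.9, 195 × 0.05 = 9.75 or 195 × 0.10 = 19.5 events.

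| c | Control events missed, r = 2% | r = 5% | r = 10% | Share lost | Recorded / true risk difference |
|---|---|---|---|---|---|
| 10% | 0.39 | 0.98 | 1.95 | 9% | 1.11 |
| 20% | 0.78 | 1.95 | 3.90 | 17% | 1.25 |
| 30% | 1.17 | 2.93 | 5.85 | 23% | 1.43 |
| 50% | 1.95 | 4.88 | 9.75 | 33% | 2.00 |

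In absolute terms the excess is r − r(1 − c) = rc. At c = 30% that is 3 percentage points when r = 10%, and 0.6 when r = 2%.

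**Step 5: direction.** Suppose a share g of GRRAND participants also have outside physiotherapy, at the same added risk r. The true difference in expected events per participant is r + rg − rc, and the recorded difference is still r. The excess is r(c − g). The bias runs against GRRAND only if outside physiotherapy is more common among controls. That is likely where the other arm already has a programme, but the protocol does not establish it.

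**The case against.** The strongest reply is that the link between the two sections is an inference. Both examples in the exclusion are anticancer treatments, so the sentence may have been meant only for expected toxicity. The other section uses a different term, governs use and not harm, and contains no cross-reference. This stands as a limit on the finding: no sentence puts physiotherapy harm either inside or outside the exclusion. It does not remove the problem, because the list of examples is open and nothing else in the article describes concomitant treatment. Sites could read it either way.

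A reader might infer that the protocol makes the same injury an adverse event in one arm and nothing in the other, so that control-arm counts are zero by rule. The documents do not support that. Outside physiotherapy taken by GRRAND participants falls under the same rule, harm from ward physiotherapy and exercise advice is untouched, and adverse events and complications are collected in both arms.

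It can also be said that the trial-relatedness filter may already remove the same events. That is fair: the exclusion may add little by itself while the filter stands, so the two must be dealt with together.

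SPADI and the health utilisation questionnaire are only partial substitutes. SPADI scores pain and disability, not events, and the questionnaire is described as recording use.

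Finally, the article condenses a fuller protocol and defers adverse-event management to the trials unit's procedures. Those may settle the point, in which case only the printed sentence needs aligning. The concern is with what that sentence states, not with missing detail.

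**Conclusion.** The point holds as an ambiguity in a stated recording rule that permits differential ascertainment. Read literally, harm from outpatient physiotherapy is recordable from GRRAND sessions and excludable from physiotherapy obtained outside allocated care. Because source is tied to arm by design, the comparison of physiotherapy- or exercise-related adverse events could be biased against GRRAND.

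The size cannot be determined from the documents. The 9% to 33% range in the table rests on assumed control-arm use of 10% to 50%, equal risk per recipient, full treatment in the GRRAND arm, no outside physiotherapy there, and complete exclusion of the control events. It is a share of physiotherapy-related events only. The share of the whole adverse-event outcome, which also includes postoperative complications, would be smaller and is unknown. The correction is worth making because it is cheap and the loss could not be repaired later.

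**What to change.** Reconcile *Safety outcomes*, *Secondary outcomes*, *Concomitant recovery treatments* and *Safety reporting, AEs and SAEs*:

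1. Limit the exclusion in *Safety outcomes* to toxicities of anticancer treatment.
2. State there that adverse events related to any physiotherapy or exercise are recorded in both arms, whoever delivered it, and that the trial-relatedness filter does not remove them.
3. Collect them with the same item at 6 weeks and 3, 6 and 12 months, with source as a data field (GRRAND session, other physiotherapy, home exercise).
4. Compare all such events between arms.

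The cost is one clarified rule and one item at follow-ups that both arms already complete, plus a few more event records to process. The source field can reveal allocation, so it should be kept from the data staff whom *Randomisation and blinding* describes as blinded. No treatment changes.
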